## Abstract

**Background:**

Interstitial lung disease encompasses a diverse group of chronic lung conditions characterised by distressing dyspnoea, fatigue, reduced exercise tolerance and poor health-related quality of life. Exercise training is one of the few treatments to induce positive changes in exercise tolerance and symptoms, however there is marked variability in response. The aetiology and severity of interstitial lung disease may influence the response to treatment. The aims of this project are to establish the impact of exercise training across the range of disease severity and to identify whether there is an optimal time for patients with interstitial lung disease to receive exercise training.

**Methods/Design:**

One hundred and sixteen participants with interstitial lung disease recruited from three tertiary institutions will be randomised to either an exercise training group (supervised exercise training twice weekly for eight weeks) or a usual care group (weekly telephone support). The 6-minute walk distance, peripheral muscle strength, health-related quality of life, dyspnoea, anxiety and depression will be measured by a blinded assessor at baseline, immediately following the intervention and at six months following the intervention. The primary outcome will be change in 6-minute walk distance following the intervention, with planned subgroup analyses for participants with idiopathic pulmonary fibrosis, dust-related interstitial lung disease and connective-tissue related interstitial lung disease. The effects of disease severity on outcomes will be evaluated using important markers of disease severity and survival, such as forced vital capacity, carbon monoxide transfer factor and pulmonary hypertension.

**Discussion:**

This trial will provide certainty regarding the role of exercise training in interstitial lung disease and will identify at what time point within the disease process this treatment is most effective. The results from this study will inform and optimise the clinical management of people with interstitial lung disease.

**Trial registration:**

Australian New Zealand Clinical Trials Registry ACTRN12611000416998

## Background

The interstitial lung diseases (ILDs) are a disabling and diverse group of chronic lung conditions that have been broadly classified into four groups: ILD of known cause such as occupational or environmental exposures and/or collagen vascular disease; granulomatous ILD such as sarcoidosis; idiopathic interstitial pneumonias including idiopathic pulmonary fibrosis (IPF) and nonspecific interstitial pneumonia (NSIP); and other rare forms of ILD including lymphangioleiomyomatosis, pulmonary Langerhans’ cell histiocytosis/histiocytosis X, and eosinophilic pneumonia [1]. Many ILDs are characterised by the development of irreversible and progressive interstitial fibrosis of the lung parenchyma [2] resulting in altered respiratory mechanics, impaired gas exchange, reduced exercise capacity and dyspnoea on exertion [3-5]. Skeletal muscle dysfunction and weakness may occur, leading to worsening exercise capacity and increasing symptoms [2,6,7]. Health-related quality of life (HRQoL) is frequently markedly reduced and those with the greatest exercise limitation report the worst quality of life [8]. As disease progresses, severe hypoxemia and pulmonary hypertension may develop [9,10], with patients often becoming dependent on supplemental oxygen.

The classification of the ILDs has been the subject of criticism, due to its failure to reflect the marked heterogeneity in clinical course within disease subgroups. Idiopathic pulmonary fibrosis (IPF), the best characterized of the ILDs, is largely a fatally progressive disease with a median survival of 3–5 years [11]. The prognosis of NSIP is more variable, and, although a minority of patients may have an accelerated decline similar to IPF [10], survival is generally significantly longer than in IPF. Dust and connective tissue disease- related ILD may be associated with a better overall survival rate but can result in significant and progressive morbidity over many years [12,13]. Prognosis of sarcoidosis is again variable and difficult to predict with stabilisation or improvement in some patients and the development of progressive pulmonary fibrosis in others [10,14].

Few treatments have demonstrated improvements in either HRQoL or community functioning for any of the ILDs [15,16]. In IPF, the most common and most lethal ILD, the options for pharmacological treatment are very limited [11]. Therapies that can improve dyspnoea, fatigue, exercise capacity and quality of life are highly sought after in ILD [16]. Exercise is one of the few treatments to show positive changes in functional capacity and symptoms. We have previously shown that exercise training could significantly improve exercise capacity and reduce dyspnoea and fatigue symptoms in patients with ILD of varying aetiology [17]. Nishiyama et al. found similar positive effects from exercise training in patients with IPF only [18]. Additionally, several observational studies evaluating the benefits of pulmonary rehabilitation, of which exercise training is an essential component, demonstrated statistically and clinically significant improvements in functional capacity, dyspnoea and HRQoL in patients with ILD of varying aetiology [19-23]. Despite these promising outcomes exercise training is not yet widely recommended for people with ILD. Only weak recommendations regarding exercise training are provided in the most recent clinical guidelines for the diagnosis and management of IPF [11] and ILD [10].

Uncertainty remains regarding the clinical relevance of exercise training across the entire range of ILDs. Patients with IPF appear to have smaller gains in functional capacity than those with ILD of other aetiology [24]. This raises the possibility that some forms of ILD may respond to exercise training better than others. Common manifestations of ILD, such as exercise induced hypoxia and pulmonary hypertension [2,9], may also affect the improvements that may be achieved. Hypoxaemia impairs maximal exercise performance [3] and pulmonary hypertension in ILD is associated with considerably reduced exercise capacity and greater exercise limitation [25-27]. In an uncontrolled study evaluating the relationship between response to exercise and disease aetiology and severity in forty-four subjects with ILD of varying aetiology, less severe lung function, less oxyhaemoglobin desaturation and less pulmonary hypertension were associated with greater improvement in functional capacity in patients with IPF [28]. This relationship persisted at six months, suggesting that those with less advanced IPF may be able to achieve sustained benefits from exercise training. This relationship was not seen in subjects with other ILDs. It is therefore possible that the timing of exercise training may be important for patients with IPF, whereas patients with other forms of ILD may benefit regardless of disease severity.

In order for exercise training to be widely adopted in clinical practice, clinicians require more information regarding its role across the disease spectrum. The aims of this study are 1) to establish the impact of exercise training on ILDs of different aetiology and severity and 2) to identify whether there is an optimal timing for exercise training to achieve maximal benefit. We hypothesise that exercise training will be effective regardless of disease severity in patients with non-IPF related ILD, whereas in patients with IPF, the response to exercise training will be greatest in those with less severe disease.

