### Sample size

One hundred and sixteen participants will be required to detect a significant difference in the primary outcome measure of change in functional exercise capacity (6-minute walk distance [6MWD]). This is based on the 80% probability of detecting a difference in the change in 6MWD between the intervention and control group using data from our previous randomised control trial [17] and Cochrane review [24]. Our sample size calculation of 116 has been powered to include the required number of participants in the three most commonly observed ILD subgroups: IPF, dust-related ILD and connective tissue disease-related ILD. To detect a true difference in the change in 6MWD in subjects with IPF, a total of 72 subjects, 36 in each group, is required. This is based on the lower limit of the range for the minimal important difference (MID) of 29m [30] with a standard deviation (SD) of 43m. To detect a true difference in the change in 6MWD between groups using the upper limit of the MID of 34m [30] with SD 43m, a total of 54 subjects, 27 in each group, would be required. In subjects with dust-related ILD, a total of 22 subjects, 11 in each group, is required. This assumes that the true difference between groups is 52m with SD of 40m. In subjects with connective tissue disease-related ILD, 22 subjects, 11 in each group, is required, assuming a difference of 38m with SD 30m.

Data from our previous study [28] indicate that to detect a relationship between carbon monoxide transfer factor (TLCO) and change in 6MWD following pulmonary rehabilitation with 80% power will require 31 subjects in the pulmonary rehabilitation group. This assumes that the true change in 6MWD is 15 meters for each 10% change in baseline percent predicted TLCO. To detect a relationship between degree of pulmonary hypertension and change in 6MWD with 80% power will require 35 subjects in the pulmonary rehabilitation group. This assumes that the true change in 6MWD is 17 meters for each 10mmHg change in baseline right ventricular systolic pressure.

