#### Statistical analysis

Data will be analysed using intention-to-treat principles, with inclusion of all available data regardless of whether the intervention is completed. The response of exercise training and control groups will be compared for change in exercise and HRQoL variables using linear mixed model analyses. Planned subgroup analyses will be conducted for participants with IPF, dust-related ILD and connective tissue-related ILD. Multiple regression analysis will be undertaken to establish which subjects respond best to exercise training and when this treatment should be offered, with change in 6MWD following exercise training as the dependent variable. Baseline demographic and physiological variables such as age; gender; disease aetiology; percent predicted TLC; percent predicted FVC; TLCO; pulmonary artery pressure; and the extent of oxyhaemoglobin desaturation during exercise will be used as predictors.

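### The severity analysis described cannot directly support the hypothesis that training works at every severity in non-IPF ILD, and any non-IPF slope would rest on about 22 trained patients

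*Protocol article*

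**What the plan says.** The hypothesis in the Background has two contrasting halves. For IPF: "in patients with IPF, the response to exercise training will be greatest in those with less severe disease". For other ILD: "We hypothesise that exercise training will be effective regardless of disease severity in patients with non-IPF related ILD". The second half follows from an earlier uncontrolled study of 44 people with mixed ILD, in which severity was related to response in IPF, and of which the article says "This relationship was not seen in subjects with other ILDs".

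Sample size treats severity as a slope to be found: "to detect a relationship between carbon monoxide transfer factor (TLCO) and change in 6MWD following pulmonary rehabilitation with 80% power will require 31 subjects". This count refers to the rehabilitation group and assumes 15 m per 10% of predicted TLCO. The article asks for 35 trained subjects for right ventricular systolic pressure, assuming 17 m per 10 mmHg. The aetiology subgroups are sized separately: 72 with IPF, then "In subjects with dust-related ILD, a total of 22 subjects, 11 in each group, is required", and the same number for connective tissue disease.

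Under Statistical analysis, "Multiple regression analysis will be undertaken to establish which subjects respond best to exercise training and when this treatment should be offered". The dependent variable is the change in 6MWD after training. Severity markers and aetiology are among the eight named predictors. The randomised subgroup comparisons are by aetiology only. Under Recruitment and randomisation, separate blocks by TLCO are listed for IPF only. The Abstract promises: "This trial will provide certainty regarding the role of exercise training in interstitial lung disease", and the closing paragraph of the Discussion repeats the promise.

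**The concern.** To say that training is effective whatever the severity is to say something about benefit over control in mild and in severe patients. A regression of change on severity among trained patients has no control comparison. It shows who changed more, not whether severe patients did better than they would have done untrained.

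What such a regression can offer the non-IPF hypothesis is a slope that does not differ significantly from zero. With few patients that result is likely even when a slope exists, and fewer evaluable patients or noisier severity markers make it more likely. At stake is the second aim, the timing of training: clinicians could be told that timing does not matter in non-IPF ILD on evidence that could not have shown otherwise.

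**Working it through.** **1. The article's group sizes.** The article gives 80% power and no alpha ("required to detect a significant difference in the primary outcome measure"). A two-sample t-test at two-sided 5% needs, per group:
- 29 m, SD 43: 35.5, so 36
- 34 m, SD 43: 26.1, so 27
- 52 m, SD 40: 10.3, so 11
- 38 m, SD 30: 10.8, so 11

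All four match the text, and one-sided 5% (28, 20, 8, 8 by the normal approximation) does not. Two-sided 5% is used below. The total is 72 + 22 + 22 = 116. Trained patients: 36 IPF and 11 + 11 = 22 non-IPF, 58 in all.

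**2. Correlation implied by 31 and 35.** The SDs of TLCO and pressure are not stated, so the slope sizes cannot be rebuilt directly. Fisher's z gives the implied correlation: atanh(r) = (1.960 + 0.842)/√(n − 3).
- TLCO: 2.802/√28 = 0.529, r = 0.485
- Pressure: 2.802/√32 = 0.495, r = 0.458

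**3. Power by group at those correlations.** Power = Φ(atanh(r)·√(n − 3) − 1.960).

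| Trained patients | TLCO | Pressure |
|---|---|---|
| 36 (IPF) | 86% | 81% |
| 22 (non-IPF) | Φ(2.308 − 1.960) = 64% | Φ(2.159 − 1.960) = 58% |

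In non-IPF, a relationship of that strength is missed 36% and 42% of the time.

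**4. Sensitivity to the SD.** Step 3 holds the correlation fixed. Suppose instead that the slope in metres is fixed and that the slope calculation used SD 43 m for change in 6MWD (assumed). The marker SDs are then 0.485 × 43/1.5 = 13.9 points of TLCO and 0.458 × 43/1.7 = 11.6 mmHg. Pooling the two non-IPF SDs gives √((40² + 30²)/2) = 35.4 m. So r = 1.5 × 13.9/35.4 = 0.589 for TLCO, and 0.557 for pressure. Power at 22 is 84% and 78%, so the misses are 16% and 22%. These are single-predictor figures. With the other seven named predictors in a 22-patient model, uncorrelated with the marker and explaining nothing further, the same case gives misses of about 32% and 39%.

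**5. Precision at 22.** With a true slope near zero, the 95% CI half-width per 10 units is 10 × 2.086 × SD/(marker SD × √21).
- TLCO: 14.1 m with SD 43; 11.6 m with SD 35.4
- Pressure: 16.9 m and 13.9 m

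The reference slopes are 15 m and 17 m. An estimate of 5 m per 10% TLCO would be non-significant in either case, yet its upper limit would be about 5 + 11.4 = 16 m to 5 + 13.9 = 19 m (residual SD reduced slightly for the 5 m slope).

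**6. The randomised comparison.** If the 44 non-IPF patients split evenly by severity, each half has 11 per arm. If the assumed subgroup effect holds in full in both halves, power per half is 83% (52 m, SD 40) or 81% (38 m, SD 30). For both halves it is 0.826² = 68% or 0.807² = 65%. A test that the effect itself changes with severity (22 v 22) is weaker, with power of 40–60% for TLCO and 36–54% for pressure over SDs of 43 to 35.4 m.

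**The case against.** Four points on the other side have force.

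- **A reader might infer that only an undetected slope could ever support the hypothesis.** That goes too far. Effective at every severity need not mean equally effective. A benefit over control in both milder and severe non-IPF patients would show it, as a superiority question that needs no margin. This stands. The article does not plan that comparison, though, so the limitation lies in the analysis as described, not in the hypothesis.
- **A reader might infer that the 31 and 35 are wrong or unmet.** They are not. The article requires them of the whole rehabilitation group, where 58 are planned, and the 36 trained IPF patients alone exceed both. Nor does it specify a model in the 22. That number applies only if the slope is fitted within non-IPF or allowed to differ by aetiology. But a single pooled slope cannot test a hypothesis that contrasts IPF with the rest.
- **A reader might infer that the authors will accept a null slope as proof.** No such rule is written, and the Background hedges its reading of the earlier study. A margin or interaction term could also sit in an analysis plan that is not shown, so its absence is not the point here. A later plan can add a better analysis, but it cannot by itself enlarge the group of 22.
- **The miss rates depend on SDs that the article does not give.** This stands. With the smaller non-IPF SDs and one predictor, they come close to the 20% that the design accepts elsewhere.

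**Conclusion.** The point holds in limited form. The severity analysis described does not directly address whether training is effective at every severity in non-IPF ILD, because it looks for a slope in change after training and does not compare training with control by severity. A non-IPF slope would rest on about 22 trained patients. It would miss a relationship of the strength implied by the article about 36% (TLCO) or 42% (pressure) of the time, or about 16% and 22% with the smaller non-IPF SDs. A non-significant slope would be weak evidence for the hypothesis, and the promised certainty is not earned for this part of the question.

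Assumptions: two-sided 5%; recruitment as planned with no dropout; either the implied correlation carries over to non-IPF, or the slope in metres and the marker SDs do, with SD 43 m behind the slope calculation. The finding does not extend to the sample-size section, whose figures are consistent with the group they refer to.

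**What to change.** In Statistical analysis:
1. Add the training-minus-control difference in change in 6MWD by baseline severity within non-IPF ILD, using all 44 patients, with 95% CIs. Use a treatment-by-TLCO term, or the TLCO <40% and ≥40% groups. The term has the advantage that non-IPF blocks are not split by TLCO, so the cell sizes are not controlled.
2. Report the non-IPF severity slope among trained patients with its 95% CI, beside 15 m per 10% TLCO and 17 m per 10 mmHg. These are reference values, not a formal equivalence margin: 15 m per 10% amounts to 45 m over 30 points of TLCO, more than the 29–34 m minimal important difference.
3. State that effectiveness regardless of severity will not be concluded from a non-significant slope.

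In the Abstract and the closing paragraph of the Discussion, soften the promise of certainty for this part of the question.

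The cost is wording and one added analysis, with no extra patients or measurements. The drawback is that the non-IPF severity result may well have to be reported as not established.

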## Methods

### Study design

This multi-centre randomised controlled trial will be conducted at Alfred Health, Austin Health and Western Health, Melbourne, Australia.

### Participants

Participants with a documented diagnosis of ILD will be recruited for this study from the Departments of Respiratory and Sleep Medicine at Alfred, Austin and Western Health. The diagnosis of ILD will be made according to established criteria. In IPF, the diagnostic criteria will be consistent with those outlined in the International Consensus Statement [11]. A surgical lung biopsy will not be required for entry into the study as it has been demonstrated that clinical and radiologic data are sufficient to distinguish between IPF and other ILDs in the hands of experienced clinicians [29]. Diagnosis of connective tissue disease will be made according to the rheumatological criteria for that disease; ILD in this setting will be diagnosed according to clinical/radiologic and lung function criteria, with lung biopsy in atypical cases. Dust-related ILD will be confirmed according to accepted criteria that include significant exposure to an agent recognised to cause ILD and radiological confirmation on high resolution computed tomography of the chest, as determined by independent radiologists.

Participants must be clinically stable, ambulant, and suffer from dyspnoea on exertion despite maximal appropriate medical treatment. Participants will be excluded if they 1) have a concurrent and predominant diagnosis of another significant respiratory disorder (for example: asthma, chronic obstructive pulmonary disease [COPD], bronchiectasis, cystic fibrosis, or lung carcinoma) which is the primary cause of their symptoms; 2) have a history of syncope on exertion; 3) are too unwell to attend the hospital for exercise training; 4) have any other co-morbidities, such as severe orthopaedic or neurological deficits or unstable cardiac disease which would prevent exercise training; 5) have participated in a pulmonary rehabilitation program within the previous 12 months.

### Sample size

One hundred and sixteen participants will be required to detect a significant difference in the primary outcome measure of change in functional exercise capacity (6-minute walk distance [6MWD]). This is based on the 80% probability of detecting a difference in the change in 6MWD between the intervention and control group using data from our previous randomised control trial [17] and Cochrane review [24]. Our sample size calculation of 116 has been powered to include the required number of participants in the three most commonly observed ILD subgroups: IPF, dust-related ILD and connective tissue disease-related ILD. To detect a true difference in the change in 6MWD in subjects with IPF, a total of 72 subjects, 36 in each group, is required. This is based on the lower limit of the range for the minimal important difference (MID) of 29m [30] with a standard deviation (SD) of 43m. To detect a true difference in the change in 6MWD between groups using the upper limit of the MID of 34m [30] with SD 43m, a total of 54 subjects, 27 in each group, would be required. In subjects with dust-related ILD, a total of 22 subjects, 11 in each group, is required. This assumes that the true difference between groups is 52m with SD of 40m. In subjects with connective tissue disease-related ILD, 22 subjects, 11 in each group, is required, assuming a difference of 38m with SD 30m.

Data from our previous study [28] indicate that to detect a relationship between carbon monoxide transfer factor (TLCO) and change in 6MWD following pulmonary rehabilitation with 80% power will require 31 subjects in the pulmonary rehabilitation group. This assumes that the true change in 6MWD is 15 meters for each 10% change in baseline percent predicted TLCO. To detect a relationship between degree of pulmonary hypertension and change in 6MWD with 80% power will require 35 subjects in the pulmonary rehabilitation group. This assumes that the true change in 6MWD is 17 meters for each 10mmHg change in baseline right ventricular systolic pressure.

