#### Outcome measures

Outcome measures will be collected at baseline, upon completion of the intervention period (nine weeks) and at six months following completion of the intervention (Figure 1). A six month follow-up period is the longest we consider to be clinically feasible without excessive loss of participants due to clinical decline and death. At baseline, data collection will include age, gender, body mass index, past medical history, smoking history, use of oxygen therapy, current pharmological treatment and all of the following outcome measures.

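### The 80% power attached to the primary comparison belongs to each of three subgroups with complete data; 116 is their sum, with no allowance for loss

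*Protocol article*

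**What the plan says.** The Sample size section opens with the total: "One hundred and sixteen participants will be required to detect a significant difference in the primary outcome measure". It then gives the basis: "This is based on the 80% probability of detecting a difference in the change in 6MWD between the intervention and control group". No difference or SD is given for that overall comparison.

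The next sentence gives a different origin for the number: "Our sample size calculation of 116 has been powered to include the required number of participants in the three most commonly observed ILD subgroups". The subgroup figures follow:

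- **IPF:** "a total of 72 subjects, 36 in each group, is required", from the "lower limit of the range for the minimal important difference (MID) of 29m [30] with a standard deviation (SD) of 43m". An alternative is also given: "upper limit of the MID of 34m [30] with SD 43m, a total of 54 subjects, 27 in each group, would be required".
- **Dust-related ILD:** "In subjects with dust-related ILD, a total of 22 subjects, 11 in each group, is required", for a difference of 52 m with SD 40 m.
- **CTD-related ILD:** also 22 (11 per arm), for 38 m with SD 30 m.

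The Abstract (Methods/Design) gives 116 as the number to be randomised. The section states no loss rate and no inflation. Under Outcome measures, six months is justified as the longest feasible follow-up "without excessive loss of participants due to clinical decline and death". Under Primary outcome measure, the primary endpoint is the change from baseline to nine weeks.

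**The concern.** Two things do not fit together.

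First, the 80% is attached to the intervention-versus-control comparison in all participants, but the number 116 comes from three separate subgroup calculations. A total assembled in that way does not have 80% power for the overall test.

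Second, if the subgroup sizes are numbers analysed and their sum equals the number randomised, the subgroup power holds only when almost every participant has a nine-week 6MWD.

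The subgroups matter here. The first aim concerns ILD of different aetiology, randomisation is stratified by subgroup, and subgroup analyses are planned. A non-significant result in nine or ten CTD patients per arm could be read as absence of benefit in a group believed to have 80% power. Conversely, a reader would take the chance of a positive primary result to be lower than the plan's own inputs imply.

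**Working it through.** **Inputs.** Differences, SDs and numbers per arm are those in the Sample size section; allocation is 1:1. Alpha and sidedness are not stated. Two-sided 5% is assumed because it reproduces every stated size; one-sided 5% (normal approximation) would need only 28, 8 and 8 per arm.

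**Formula.** Two-sample t-test with n per arm, 2n − 2 degrees of freedom and noncentrality (Δ/SD) × √(n/2).

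**Step 1. Reproduce the plan's sizes (80% power).**

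| Group | Δ/SD | n per arm needed | Stated |
|---|---|---|---|
| IPF, 29 m | 29/43 = 0.674 | 35.5 → 36 | 36 |
| IPF, 34 m | 34/43 = 0.791 | 26.1 → 27 | 27 |
| Dust | 52/40 = 1.300 | 10.3 → 11 | 11 |
| CTD | 38/30 = 1.267 | 10.8 → 11 | 11 |

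All four match. The stated sizes are the smallest whole numbers analysed that reach 80%.

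**Step 2. The total.** 72 + 22 + 22 = 116, which is exactly the number randomised. Nothing has been added for loss.

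**Step 3. Subgroup power with complete data.** Noncentrality is 0.674 × √18 = 2.86 for IPF, 1.300 × √5.5 = 3.05 for dust and 1.267 × √5.5 = 2.97 for CTD. Power is 80.6%, 82.6% and 80.7%.

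**Step 4. Subgroup power with a few patients missing.**

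| Missing in the subgroup | IPF | Dust | CTD |
|---|---|---|---|
| One patient in total | 79.99% | 80.6% | 78.5% |
| One patient per arm | 79.4% | 78.5% | 76.4% |

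**Step 5. The overall comparison.** The plan gives no overall effect, so take its smallest difference (29 m) and its largest SD (43 m). With 58 per arm, noncentrality is 0.674 × √29 = 3.63 and power is 95.0%. At 34 m with SD 43 m it is 98.8%. With 58 per arm and SD 43 m, 80% power corresponds to a difference of 22.6 m. Equivalently, for 29 m the SD would have to be about 29 × 43/22.6 = 55 m before power fell to 80%.

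**Step 6. Power by loss rate.** The rates are assumptions. Expected numbers per arm are n × (1 − loss) and may be fractional.

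| Loss at nine weeks | Overall (29 m, SD 43 m) | IPF | Dust | CTD |
|---|---|---|---|---|
| 0% | 95.0% | 80.6% | 82.6% | 80.7% |
| 5% | 93.9% | 78.5% | 80.5% | 78.4% |
| 10% | 92.7% | 76.2% | 78.0% | 75.9% |
| 15% | 91.2% | 73.7% | 75.4% | 73.2% |
| 20% | 89.5% | 71.1% | 72.5% | 70.2% |

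**The case against.** The case on the other side has several parts.

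- **The arithmetic is right.** Every stated size reproduces. This stands: the defect lies in what the 80% is said to describe and in the missing margin, not in a miscalculation.
- **The text already says that 116 was built to fill three subgroups.** A reader can add 72, 22 and 22. This is true, but the two preceding sentences assign 116 and the 80% to the overall comparison, and the section never separates the two.
- **The remark on decline and death concerns six months, not nine weeks.** This stands. Participants must be clinically stable and those too unwell to attend are excluded, so nine-week loss may be small. A reader might infer that the plan itself expects heavy loss at the primary time point; it does not say so.
- **IPF has some reserve.** If the true difference is 34 m, 27 per arm suffice, so 36 per arm tolerate 25% loss (36 × 0.75 = 27). This holds for IPF under the larger effect only. Dust and CTD have no such alternative in the text.
- **By the normal approximation, one loss per arm still leaves 80.5%, 82.8% and 80.9%.** That approximation gives 35, 10 and 10 per arm, not the stated 36, 11 and 11. The t-test is what matches the plan, and it is the more accurate at 11 per arm.
- **The mixed model uses all available data.** It may recover some precision, but the stated calculation does not rely on it.

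A reader might also infer that each subgroup drops below 80% as soon as any single patient is missing. That is too strong: dust keeps 80.6% and IPF is 79.99%; only CTD clearly falls.

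**Conclusion.** The point holds in this form. The Sample size section attaches 80% power to the overall primary comparison, although the calculation behind 116 gives about 80% to each of three subgroups when every participant is analysed. The overall comparison has about 95% power at the plan's smallest difference and largest SD, and about 90% after 20% loss. Each subgroup is below 80% once one patient per arm is missing. At an assumed 10% loss the figures are about 76% (IPF), 78% (dust) and 76% (CTD); at an assumed 20%, about 71%, 72% and 70%.

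Two further readings are not supported. The primary comparison is not underpowered; its power is understated. Nor does the plan promise significance in all three subgroups at once. With complete data that chance is about 0.806 × 0.826 × 0.807 = 54%, but joint success is not a criterion anywhere in the document, so the figure is no measure of a failing.

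The conclusion rests on a two-sided 5% t-test (unstated, but it reproduces all the sizes), on the plan's own differences and SDs, and on loss rates that are assumed because no nine-week rate is given.

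**What to change.** Keep 116 and restate the Sample size section so that it:

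1. says that 116 is the sum of the subgroup requirements (72 + 22 + 22);
2. says that 80% is the approximate power of each subgroup comparison with complete nine-week data, and not that of the overall primary comparison;
3. states alpha and sidedness;
4. gives the power of the overall comparison with the difference and SD used, and the power of each subgroup at the number expected to be analysed at nine weeks. If no loss rate can be justified, a short table over 0% to 20%, like the last one in the working, will do.

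The cost is a rewritten paragraph and no extra patients. The drawback is that the stated subgroup power becomes less favourable. The rewording does not raise that power; it only stops a non-significant subgroup result from being read against a power the subgroup may not have had.
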